## Abstract

**Background::**

Despite family carepartners of individuals post-stroke experiencing high levels of strain and reduced quality of life, stroke rehabilitation interventions rarely address carepartner well-being or offer training to support their engagement in therapeutic activities. Our group has developed creative intervention approaches to support families during stroke recovery, thereby improving physical and psychosocial outcomes for both carepartners and stroke survivors. The purpose of this preliminary clinical trial is to test the feasibility of an adapted, home-based intervention (Carepartner Collaborative Integrative Therapy for Gait-CARE-CITE-Gait) designed to facilitate positive carepartner involvement during home-based training targeting gait and mobility.

**Methods::**

This two-phased study will determine the feasibility of CARE-CITE-Gait, a novel intervention developed by our team that leverages principles from our previous carepartner-focused upper extremity intervention. During the 4-week CARE-CITE-Gait intervention, carepartners review online video-based modules designed to illustrate strategies for an autonomy-supportive environment during functional mobility task practice, and the study team completes two 2-hour (home-based) visits for dyad collaborative goal setting. In Phase I, the usability and acceptability of the CARE-CITE-Gait modules will be evaluated by stroke rehabilitation content experts and carepartners. In Phase II, feasibility (based on measures of recruitment, retention, and intervention adherence) will be measured. Preliminary effects of the CARE-CITE-Gait will be gathered using a single-group, evaluator blinded, quasi-experimental design with repeated measures (two baseline visits one week apart, post-test, and one-month follow-up) with 15 carepartner and stroke survivor dyads. Outcomes include psychosocial variables (strain, family conflict surrounding stroke recovery, autonomy support and life changes) collected from carepartners, and measures of functional mobility, gait speed, stepping activity, and health-related quality of life collected from stroke survivors.

**Discussion::**

The findings of the feasibility testing and preliminary data on the effects of CARE-CITE-Gait will provide justification and information to guide a future definitive randomized clinical trial. The knowledge gained from this study will enhance our understanding of and aid the development of rehabilitation approaches that address both carepartner and stroke survivor needs during the stroke recovery process.

**Trial Registration::**

ClinicalTrials.gov, NCT 05257928. Registered 25 February 2022, https://clinicaltrials.gov/ct2/show/NCT05257928

## Background

Recognized as an independent risk factor for other co-morbidities and a recurrent stroke,[1] reduced physical inactivity in stroke survivors (SS) is a critical area of rehabilitation focus.[2] Even after discharge from rehabilitation, a large proportion of stroke survivors continue to have persistent impairments in gait and balance, which in turn reduce community ambulation and adversely affect quality of life. Few SS meet the current American Stroke Association guidelines[3] of 20–60 minutes of aerobic exercise 3 to 5 days per week. Typically, SS achieve only 63% of the recommended steps per day for people with disability (4078 versus 6500–8500).[4] Fini et., al.[2] cite motivation and carepartner (CP) support as potential factors to consider, underscoring self-management and behavior change to enhance engagement and sustainability of post-stroke physical activity programs. However, lacking training and preparation to support the complexities of stroke rehabilitation,[5–7] CPs can experience high levels of care burden, reduced quality of life, and family conflict surrounding the post-stroke recovery process [8,9].

Because the physical, emotional, and psychological aspects of their daily living are intricately interconnected, CP’s well-being can impact the health outcomes of both CPs and SSs. With earlier discharge and a greater proportion of rehabilitation occurring at home, it is critical to find strategies to enable CPs to support rehabilitation at home and in the community without adding to their own caregiving burden. Previous research studies incorporating CP training during SS rehabilitation have had promising results. [10, 11] The London Stroke Carers Training Course, a comprehensive competency training for CPs, reduced health and social care costs, improved QOL, and reduced CP burden, [11] but these findings were not replicated in a multi-site study.[12] Work by Creasy et. al.[13] suggests that CPs are keenly aware of the critical nature of their role in the care of their loved one and that they have expectations of being included in post-stroke treatment planning. CPs underscored their need to have greater information about stroke and customization of rehabilitation training to more accurately address specific family needs. [14] Several studies have shown that improving CP coping and life skills to care for a chronically ill family member leads to decreased caregiver burden and improved QOL[15, 16] [17]. Supporting previous summary recommendations [7, 17], a recent systematic review of stroke family CP and dyad interventions[18] emphasized that these interventions should combine skill building (e.g., problem-solving, goal setting, and stress management) with psychoeducational strategies and should be tailored to individualized needs of the CP. Engagement of CPs offers valuable opportunities to enhance rehabilitation therapies.

If therapeutic interventions are delivered in a vacuum without consideration of family context, a fundamental cornerstone influencing successful stroke recovery is overlooked. To address this critical gap, our team developed a theory-based, task-specific, and CP-focused intervention - **Care**partner and **C**ollaborative **I**ntegrated **T**h**e**rapy (**CARE-CITE**)[19], The initial version of CARE-CITE was designed to enhance upper extremity (UE) functional task practice in the home setting by instructing CPs in methods for collaborative goal setting and creating an autonomy-supportive environment. Arising from Self-Determination Theory[20], CARE-CITE uses web-based interactive modules with exemplary videos of actual stroke dyads (CP and SS) demonstrating collaborative problem-solving during activities of daily living and modeling autonomy-supportive dialogue that offers choice, rationale, providing empathy, and avoids controlling language. Preliminary studies show the feasibility[21] and promising therapeutic benefits of CARE-CITE in CPs and SS coupled with UE constraint-induced movement therapy (CIMT), another evidence-supported UE intervention. In a two-group randomized pilot study (n = 32 dyads), we compared a CARE-CITE with CIMT group to a CIMT-alone group of SS who had completed formal rehabilitation therapy.[22] Both groups received 10 sessions of home-based CIMT, but only CPs in the CARE-CITE with CIMT group reviewed the online CARE-CITE modules. Importantly, in our baseline data with these SSs in the chronic phase of stroke, [22] we found that the majority of CPs continue to experience family conflict surrounding stroke recovery, potentially influencing SS motivation and adherence. Higher levels of conflict around stroke recovery were related to higher levels of CP strain and less autonomy support provided to the SS for rehabilitation activities. Outcomes from the study showed promising trends indicating CP’s receiving CARE-CITE had improved psychosocial outcomes (significant within-group CP changes were found for CIMT + CARE-CITE but not CIMT-alone), showed positive quality of life changes, with less strain, fatigue, and family conflict around stroke recovery. [23,24] In both groups SS upper extremity (UE) function and health-related quality of life (hrQOL) improved.[24] However, only the CARE-CITE + CIMT group maintained or continued to improve UE function. These results suggest that CP engagement may be an important factor in the continued support of functional progress in rehabilitation.

The COVID-19 pandemic has revealed both an urgent need and opportunity to craft multiple modes of delivery for interventions for families after stroke, in particular the development of telerehabilitation approaches.[18, 25] Web-based approaches like CARE-CITE-Gait increase accessibility to content outside of traditional clinic hours and reduce transportation-related barriers. While many CP may still lack resources and skills to use web-based approaches, the pandemic has rapidly increased the adoption of these technologies and a recent study [26] found that 86.1 % of SS and CP had internet access. Implementing telerehabilitation delivery of CP interventions offers promising and scalable alternatives to improve access to care.

Responding to the insights gained from the engagement of the CP in UE rehabilitation and the increasing need for telerehabilitation, we now seek to broaden the scope of our intervention and further optimize post-stroke recovery by pairing CARE-CITE with home-based gait and functional mobility training (CARE-CITE-Gait). Physical inactivity resulting after stroke has been associated with physical and psychosocial problems,[27] including increased risk of recurrent stroke. Despite being a critical and modifiable risk factor,[1] most SS do not engage in enough physical activity to meet the American Stroke Association guidelines.[3] In addition to physical impairments (such as balance and weakness) impacting physical activity, other important factors include SS mood, motivation, and CP involvement. [2] Designing interventions that support physical activity by engaging family CPs may be a key factor for the sustainability of health-related behaviors.

In the current study, we are modifying our existing CARE-CITE intervention to address gait and functional mobility, and test 4 weeks of CARE-CITE-Gait in 15 CP and SS dyads. The aim of this paper is to describe the CARE-CITE-Gait, two-phased, feasibility study design. The objective of Phase I of this trial is to evaluate the content validity and user satisfaction (usability and acceptability) of the CARE-CITE-Gait intervention by CPs and stroke rehabilitation content experts. The primary objective of Phase II is to determine the feasibility of CARE-CITE-Gait for SS and CP dyads, as indicated by participant recruitment and retention, SS and CP adherence to the intervention, CP usability and satisfaction with the CARE-CITE-Gait modules, and safety (occurrence of SS adverse events). The secondary objective of Phase II is to determine the preliminary effects of the CARE-CITE-Gait intervention on SS and CPs. Psychosocial outcomes will be measured for the CP, including family conflict about stroke recovery, strain, autonomy support, and positive life changes. Outcomes measured from the SS include functional mobility, gait speed, stepping activity, and health-related quality of life (hrQOL).

## Methods

Identification and reporting of relevant elements of this protocol are based on the Standard Protocol Items: Recommendations for Intervention Trials (SPIRIT) checklist [28] and Template for Intervention Description and Replication (TIDieR) guidelines for intervention descriptions [29]. This is the first published version of this clinical trial study protocol [11.17.2018]. Any protocol amendments will be immediately reported to University Internal Review Board for approval and to funding agency as appropriate.

### Approvals

Ethical approval was obtained by Emory University Institutional Review Board and this protocol is registered on clinicaltrials.gov (NCT05257928).

### Study Design & Setting

In Phase I, stroke rehabilitation content experts and CPs will evaluate the usability and acceptability of the CARE-CITE-Gait modules. In Phase II, feasibility (based on measures of recruitment, retention, and intervention adherence) and preliminary effects of CARE-CITE-Gait will be measured using a one-group, quasi-experimental design with repeated measures (two baseline visits one week apart, post-test, and one-month follow-up) with 15 CP and SS dyads. While the in-person portion of the intervention will take place in participant homes, the study recruitment, screening, and evaluations (evaluator-blinded) for CP and SS dyads, will occur in a stroke research laboratory within an urban rehabilitation hospital located in Atlanta, Georgia, United States (Figure 1 Consort Flow Chart: Evaluation of Carepartner-Integrated Telehealth Gait Rehabilitation Program for Persons with Stroke (CARE-CITE-Gait) N=15)). Licensed physical therapists will conduct the evaluations and administer the 4-week home-based CARE-CITE-Gait intervention. During the intervention period, the web-based CARE-CITE-Gait modules will be accessed online by CPs independent of therapist involvement. The study schedule schematic design is presented in Table 1.

### Recruitment

#### Participants

Expanding on the established validity and satisfaction demonstrated for the original upper extremity CARE-CITE intervention [21], for Phase I of the study, six to seven stroke rehabilitation clinicians and research content experts will evaluate the content validity of CARE-CITE-Gait adaption of the upper extremity functional tasks to gait and mobility focused examples. Three CPs will provide initial feedback regarding satisfaction (usefulness, ease of use, and acceptability) to guide any additional refinements before the initiation of Phase II.

For Phase II of this study, 15 SS and CP dyads will be recruited. Both CP and SS must be greater than 21 years of age, able to read and write English, and able to provide informed consent.

Inclusion criteria for the SS include:
> 3 months post ischemic or hemorrhagic stroke eventDischarged from inpatient neurologic rehabilitation to their homeAble to walk 10-meters with or without an assistive devicePresence of CP

Exclusion criteria for SS include:
Severe cognitive deficits (as indicated by Mini-mental test ≤ 24)Concurrent participation in other rehabilitation intervention research trialsPhysician determined major medical or musculoskeletal problems that would limit study participation

CPs will be self-identified as a spouse/partner or family member dwelling in the same household who has the role as the primary caregiver of the SS. The primary CP inclusion criteria include interest and willingness to support the SS during the study period activities, ability to provide any necessary supervision with safety-related mobility activities, and no significant cognitive deficits (as demonstrated by their ability to explain the study purpose and their CP role to the PI during the informed consent discussion). Participants will be requested not to participate in other research studies during the study intervention and evaluation period.

#### Recruitment and retention strategies

Through weekly monitoring of the inpatient and outpatient rehabilitation stroke census, potential participants will be identified by study staff and eligibility criteria will be confirmed based on physician and physical therapy electronic medical records. To broaden recruitment outreach, the PI (SB) and Co-I (TK) will provide stroke information in services to other regional hospitals and community support groups and will partner with other stroke research collaborators in the region to facilitate shared recruitment efforts. The project coordinator will screen interested dyads to confirm eligibility and schedule enrollment. Targeted enrollment rate is two-three dyads per month. To support participant adherence and retention, the project coordinator and PI will be available to respond promptly to any participant concern or issue (via email or phone) and will provide regular check in telephone calls or texts for appointment confirmation reminders. Each study participant receives $50 ($100/dyad) for study participation.

#### Sample size estimation

For Phase II, given the time required to adapt the intervention, the proposal timeline, and preliminary data from our upper extremity intervention, a sample size of 15 dyads is proposed to evaluate feasibility (2-3 dyads/month). An attrition rate of ~8% is projected based on the literature and our previous work [30]; thus, we will enroll 16 dyads to achieve a final sample of 15. Assuming a two-tailed alpha=0.05, we will have 80% power to detect an effect size=0.78 (Cohen, large), and can calculate 95% confidence intervals within 0.64 standard deviations. These data will provide precision to the estimates of mean changes, variability, and effect sizes for key outcomes. Importantly, these data will inform sample size estimation and identify feasibility lessons to guide our planned next step - a randomized clinical trial evaluating the efficacy of CARE-CITE-Gait.

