Standard data cleaning, identification of missing data, and internal consistency reliability for standardized scales will be completed. We will investigate whether missing data is related to treatment and baseline factors but do not anticipate missing data being a limitation if lost-to-follow-up rates in this new clinical trial are similar to other stroke studies performed in the PI (SB) and Co-I (TK) labs. Primary quantitative statistical analyses will be performed by the study statistician (GC) using SAS statistics for Windows (Version 9.4) and accelerometry data analysis (SS stepping activity) will be performed by lead research assistant (RS) using ActiLife software (Version 6.13.4). Descriptive statistics (e.g., frequencies, means, ranges, standard deviations) will be calculated for all relevant variables, as well as to identify unusual or suspect values requiring review and confirmation. Additional descriptive statistics will be calculated for feasibility measures of recruitment rate, retention, and CP usability and satisfaction with CARE-CITE-Gait (described under Feasibility section). To determine estimates of variability (for postulating effect sizes to design next phase clinical trials, the mean and median changes from baseline to one month and standard errors of the means will be calculated. To provide preliminary information about possible feasibility study intervention effects, confidence intervals for the difference in mean changes for major study variables will be reported as descriptive statistics. Graphical methods will be used to investigate outliers and investigate the consistency of the changes over time. Estimates of inter-correlations among the study variables will be calculated to gain insight into potential variables that could influence response to the intervention and guide the design of future studies. To understand potential relationships and possible confounding factors we will examine SS co-morbidities (e.g., history of testing positive for COVID) and the biological variables of CP age, sex, gender and relationship of CP to SS (e.g. spouse, adult child). The second phase of the analysis will include one-way repeated measures analysis of variance (ANOVA) to evaluate differences between baseline, post, and follow-up timepoints. Tukey’s pairwise comparisons will be used to determine which time points are different if necessary. Level of significance of 0.05 will be used. No adjustments will be used to control for multiple study variables.

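### The 95% interval precision of 0.64 SD is not the ordinary figure for 15 dyads (0.55 SD) and is not on the same basis as the 0.78 SD detectable effect beside it

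*Protocol article*

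**What the plan says.** The Sample size estimation section states that "a sample size of 15 dyads is proposed to evaluate feasibility" and gives adaptation time, the project timeline and earlier data as the reasons. On losses it says "An attrition rate of ~8% is projected", and so "we will enroll 16 dyads to achieve a final sample of 15".

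One sentence then says what this sample delivers. It opens with "Assuming a two-tailed alpha=0.05" and continues "we will have 80% power to detect an effect size=0.78 (Cohen, large"). It ends by saying that the team "can calculate 95% confidence intervals within 0.64 standard deviations". The section names no test, interval method, SD scale, assurance probability or multiplicity adjustment for either figure.

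Two other places bear on the reading. Study Design & Setting describes the effects as measured "using a one-group, quasi-experimental design with repeated measures", so the natural quantity is a within-person mean change. Data management and analysis says that "confidence intervals for the difference in mean changes for major study variables will be reported as descriptive statistics". The repeated-measures ANOVA over baseline, post-test and follow-up, with Tukey comparisons where needed, comes afterwards as a separate second phase.

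**The concern.** A detectable effect and an interval half-width for the same mean change, sample and alpha are tied together: both are multiples of SD/√n. Given one, the other follows. Here the first figure identifies the sample and method cleanly, and the second does not follow from it.

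The stake is modest. The section says that the data will give precision to the estimates of mean change and inform the sample size of the next randomized trial, and 0.64 is the only numerical statement of precision in the article. A reader who relies on it will take the intervals to be wider than an ordinary analysis of 15 dyads gives, or will be unable to tell which calculation lies behind it.

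**Working it through.** **Inputs** (Sample size estimation, protocol article): final n = 15, two-sided alpha 0.05, power 80%, stated effect 0.78, stated interval precision 0.64 SD. The one-group design is from Study Design & Setting. Enrolment of 16 with 8% attrition gives 16 × 0.92 = 14.7, consistent with 15.

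**1. Reproduce the power figure.** Paired (one-sample) t-test on change, noncentral t with 14 degrees of freedom and noncentrality d√15.
- Effect detectable with 80% power: d = 0.778.
- Power at d = 0.78: 0.802.

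So 0.78 is the ordinary, unadjusted figure for n = 15, in units of the SD of within-person change.

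**2. Interval half-width for the same n and method.**
- Formula: t(0.975, n−1)/√n, in SDs of change.
- n = 15: 2.145/3.873 = 0.554.
- With z in place of t: 1.96/3.873 = 0.506.
- Stated against computed: 0.64/0.554 = 1.16, so the stated half-width is about 16% wider.

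**3. Could another n give both figures?**

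| n | 95% half-width (SD) | effect at 80% power (SD) | ratio |
|---|---|---|---|
| 12 | 0.635 | 0.889 | 1.40 |
| 13 | 0.604 | 0.847 | 1.40 |
| 14 | 0.577 | 0.810 | 1.40 |
| 15 | 0.554 | 0.778 | 1.40 |
| 16 | 0.533 | 0.750 | 1.41 |

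The ratio of detectable effect to half-width lies between about 1.39 and 1.41 for every n from 9 to 17. The document's ratio is 0.78/0.64 = 1.22. Rescaling both figures to a different SD leaves the ratio unchanged. So within that range no single n, and no common SD scale, gives both figures by the ordinary method.

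**4. What does give about 0.64?**
- Ordinary interval, n = 12: 0.635.
- Tukey simultaneous interval, three time points, n = 15: q(0.95; 3, 28)/√2 = 2.474, and 2.474/√15 = 0.639.
- Bonferroni for two comparisons, n = 15: 0.648.
- Half-width not exceeded with 80% probability, n = 15: 0.631 (0.634 conditional on the interval covering the true value).
- Half-width in raw-score SDs, n = 15: 0.554 × √(2(1−ρ)) = 0.64 needs a pre-post correlation ρ of 0.33, which the article does not state. It would also put the two figures on different scales.

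**The case against.** The strongest reply is that 0.64 can be right for 15 dyads. The sentence uses the language of a bound and does not call 0.64 an expected half-width. At n = 15 the half-width stays at or below 0.64 SD with probability 0.82; at n = 14 that probability is 0.75. So 15 is the smallest sample that meets 0.64 with at least 80% probability, and 80% is the power level in the same sentence. Tukey over three time points is a second route (0.639), and the article does plan Tukey comparisons. A condensed article may also leave the interval method to the full protocol.

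Much of this stands. It cannot be said that 0.64 is impossible with 15 dyads, and the absence of a named method is not in itself a fault in an article. What does not stand is the idea that the printed figure can be read as it is. An unqualified 95% interval is ordinarily the t interval, nothing in the section points to assurance or Tukey, and the analysis section keeps the descriptive intervals apart from the Tukey step.

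Three stronger readings may tempt a reader, and the article supports none of them:
- **That 0.78 is too optimistic and should be 0.86 or 0.89.** Those are the 80%-power effects under Tukey-adjusted testing at n = 15 and under n = 12. The article assumes neither for power, and 0.78 is correct for the stated 15. If 0.64 is an assurance bound, both figures are right for 15.
- **That the plan really expects 12 or 13 completers.** It projects 15. The 85% and 80% retention values in Table 3 are acceptance thresholds, not forecasts.
- **That the sample size rests on the wrong figure.** The 15 dyads are justified by timeline, adaptation time and earlier data for judging feasibility. The two figures describe what that number delivers.

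**Conclusion.** The point holds as a minor error. By the ordinary method, 15 dyads give a 95% half-width of 0.55 SD of within-person change, and the stated 0.64 is about 16% wider. The detectable effect of 0.78 is correct and identifies the method, so the two figures in the sentence are not on the same basis.

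The direction is conservative: 0.55 lies inside 0.64, so the plan understates its precision. No design decision depends on the figure, Phase II is primarily a feasibility study, and the intervals are descriptive.

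This rests on two assumptions: that the interval meant is the usual t interval for a mean change, and that the SD is that of the within-person change, the scale on which 0.78 also reproduces. If 0.64 was calculated as a simultaneous or assurance bound, the defect shrinks to an unlabelled method. The article does not allow a reader to decide between these origins.

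**What to change.** Change one sentence in Sample size estimation, in one of two ways:
- Give both figures for n = 15 on the same basis: 80% power to detect a mean change of 0.78 SD, and a 95% confidence interval half-width of 0.55 SD, both in units of the SD of within-person change.
- If 0.64 was intended as a simultaneous or assurance bound, keep it and name the method, the number of comparisons or the assurance probability, and the SD scale.

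Optionally, add the values at the lowest retention that Table 3 accepts at one month. 80% of 16 is 12.8, about 13 dyads, with a half-width of 0.60 and a detectable effect of 0.85. Label this as the accepted minimum, not the expected number of completers.

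The cost is a wording change. Sample size, procedures and analyses stay as they are.
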